| Demographic Variables                                                                                                                                                                                                                                                                                                                                                                                                                                                                                                                                                                                                                                                                                                                                                                                                                                                                                                                                                                                                                                                                                                                                                                                                                                                                                                                                                      | Age in years, gender, order of born, type of family education, religion, locality of residence, monthly income of parents (in rupees), occupation of father and mother, educational status of father and mother, family history, and source of information on Atherosclerosis | Structured questionnaire                              |  |
| 
3.5 Setting:
 
The study setting is selected schools at Arakonam, Vellore District, Tamil Nadu State, India.
 
3.6 Population
 
All adolescents who are 15 to 17 years of age, studying in 10th to 12th standard in Higher Secondary Schools are the population for the present study.
 
3.6.1 Target Population
 
It refers to all middle age adolescent students who are studying in Higher Secondary Schools during the study period belonging to 10th to 12th standard at Tamil Nadu.
 
3.6.2 Accessible Population
 
It refers to the aggregate of adolescents with whom the designated criteria are conformed and accessible to the investigator. Thus, the accessible population is 3 Higher Secondary Schools, a total number of adolescents who are studying in 10th to 12th standards at Arakonam, Vellore district, Tamil Nadu.
 
3.7 Sampling
 
3.7.1 Sample
 
In the current study, the adolescents who are studying in 10th to 12th standards who fulfilled the inclusive criteria are the study participants.
 
3.7.2 Sample selection criteria
 
Inclusion criteria
 
v Middle age adolescence who are studying in higher secondary schools aged between 15-17 years at Arakonam.
 |                                                                                                                                                                                                                                                                               |                                                       |  |

[figure not shown]

v Middle age adolescence who are willing to participate in the study

v Able to understand English and Tamil

v Both genders are included in the study

v BMI above 50th percentile

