| Intervention | Structured interventional strategy, Physical activity, reduction in sedentary activity and healthy dietary habit tips. | Research approach: Quantitative Research
Approach Research design: Pre-experimental one group pre-post test time series research design. O1 x1 O2 x2 O3 x3 O4 O1 - Observation at the pre-test (Baseline) x1 - Structured interventional strategy, Physical activity (skipping and walking including warm-up and rest) for 30 minutes, reduction in sedentary activity and healthy dietary habit tips by booklet and newsletter to parents. O2 - Observation after 4 weeks x2 - Structured interventional strategy, Physical activity (skipping, walking, running, and dancing including warm-up and rest) for 45 minutes, reduction in sedentary activity and healthy dietary habit tips by booklet and newsletter to parents. O3 - Observation after 8 weeks x3 - Structured interventional strategy, Physical activity (skipping, walking, |

[figure not shown]

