| Comparator Agent | NIL                                                                                                                    | NIL                                                                                                                                                                                                                                                                                                                                                                                                                                                                                                                                                                                                                                                                                                                                                                                                                                                                                                                                                                                                                                                                                                                                                                                                                                                                                                                                                                                                                                                                                                                                                              |

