| Method of Generating Random Sequence | Stratified randomization                                                                                                                                                                                                                                                                                                                                                                                                                                                                                                                                                                                                                                                                                                                                                                                                                                                                                                                                                             |                                                                                                                                                                                                                                                                                                                           |

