**Main outcome measure:** Primary outcomes will be assessed at 4th week, 8th week, and 12th week post intervention are BMI and physical activity. Secondary outcomes are dietary intake and sedentary activity will be assessed at 4th week, 8th week, and 12th week post intervention.

**Conclusions:** Structured interventional strategy can improve primary and secondary outcomes among middle age adolescence.

**Discussion:** This study will provide whether integration of knowledge on Atherosclerotic risk factors improved by structured interventional strategy, promoting good dietary habit messages to prevent atherosclerotic risk factors, and how to decrease secondary activity. Physical activity levels are remarkably very low among middle age adolescents, this study provides feasible with low cost intervention to be effective in schools, the learned behavior can be implemented throughout the life of an individuals and also sharing their experience with peers, family members and part of their community.

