| 
This study was to estimate CV risk in apparently healthy adolescent girls and aimed to test some new, emerging CV risk factors and their interaction with the traditional ones, such as obesity. To assess the impact of low bilirubin levels, as a routine biochemical parameter, as an additional risk factor for atherosclerotic disease in the adult phase. 45 obese adolescent girls and 45 age- and sex-matched normal weight controls, all nonsmokers, mean age 17.8±1.22 years were included. Anthropometric and biochemical parameters were measured. Cardiovascular Risk Score (CVRS) was calculated by adding the points for each risk factor (e.g. sex, HDL-c, non-HDL-Cholesterol (HDL-c), blood pressure and fasting glycemia). Results stated that a significant positive relationship between CVRS and ALT, high sensitivity CRP and TG/HDL-c, but an opposite relationship between CVRS and total bilirubin were found (P<0.001). Higher waist circumference (WC) and LDL-c, but lower HDL-c were independent predictors of lower bilirubin values (P<0.001). Concluded that the obese adolescent girls increased risk of cardiovascular disease late in life. In addition to the traditional risk factors, total bilirubin may have the potential to discriminate between low and higher risk for cardiovascular disturbances in healthy adolescent girls (Kisic et al., 2016).
 
A prospective cohort Shanghai Women's Health Study (SWHS) to investigate adolescent exercise in association with cancer, cardiovascular (CVD), and all-cause mortality among middle-aged and older women. 74,941 Chinese women aged 40–70 years recruited 1996–2000. In-person interviews at enrollment assessed adolescent and adult exercise history, medical and reproductive history and other lifestyle and socioeconomic (SES) factors. Mortality follow-up occurs via annual linkage to the Shanghai Vital Statistics Registry. Result stated that adjusting for birth year and other adolescent factors, adolescent exercise was associated with reduced risk of CVD. Results were attenuated after adjustment for adult SES and lifestyle factors. Participation in sports teams was inversely associated with cancer mortality (95% CI: 0.66(0.76–0.97)). Joint adolescent and adult exercise was associated with reduced risk of all-cause and CVD mortality (HRs (95% CIs): 0.80(0.72–0.89) and 0.83(0.69–1.00). Concluded that adolescent exercise participation, independent of adult exercise, was associated with reduced risk of CVD, and all-cause mortality (Nechuta et al., 2015).
 
In the Young Finns Study Improvement in HDL-cholesterol/LDL-cholesterol ratio and obesity from childhood to adulthood was associated with reduced CIMT progression. However, carotid intima-media thickness (CIMT) still progressed more than in participants who had normal baseline and follow-up HDL-cholesterol/ LDL-cholesterol ratio and BMI. Frequent fruit intake and physical activity in childhood were also associated with lower adult CIMT. Similarly, the number of CVD risk factors in childhood and adulthood were associated with increased pulse wave velocity in adulthood, but reduction in the number of risk factors and improvement in BMI over time were associated with lower pulse wave velocity in adulthood. Pediatric lifestyle remains important, these data also suggest that vascular changes in childhood can at least be improved with appropriate improvement in CVD risk factors during young adulthood (Juonala et al., 2010).
 
A prospective study corroborated to estimate population-level trajectory groups of life course cardiovascular risk to explore their impact on mid-life atherosclerotic and metabolic outcomes among Bogalusa Heart participants n=1,265, between the mean ages of 5.6–48.3 years, each with at least 4 study visits from childhood in 1973 through adulthood in 2016. Outcomes included mid-life subclinical atherosclerotic measures [carotid intima-media thickness (cIMT), pulse wave velocity (PWV)], metabolic indicators [diabetes and body mass index (BMI)], and short physical performance battery (SPPB). Adult metabolic and vascular outcomes were significantly determined by life course cardiovascular risk trajectory groups (all p<0.01). Those in the High-Low group had lower risks of diabetes (20% vs. 28%, respectively; p= .12) and lower BMIs (32.4 kg/m^2 vs. 34.6 kg/m^2; p=0.06) than those who remained at high risk (High-High) throughout life. However, the High-Low group had better cIMT (0.89 mm vs. 1.05 mm; p<.0001) and PWV (7.8 m/s vs. 8.2 m/s; p=0.03) than the High-High group. For all outcomes, those in the Low-Low group fared best. Concluded that considerable movement between low and high relative cardiovascular risk strata over the life course. Children who improved their relative cardiovascular risk over the life course achieved better mid-life atherosclerotic health despite maintaining relatively poor metabolic health through adulthood (Pollock et al., 2019).
 
A study to aimed to study the association between serum ferritin levels and dyslipidemia in adolescents, because dyslipidemia is considered an important modifiable cardiovascular risk factor in the young 1,879 subjects (1,026 boys and 853 girls) from the 2009–2010 Korean National Health and Nutrition Examination Survey IV. Subjects were categorized into quartiles according to their lipid parameters, which were classified according to age and gender. Those in the highest quartile groups for total cholesterol, low-density lipoprotein cholesterol (LDL-C), and triglyceride concentrations were diagnosed as having dyslipidemia. Those in the lowest quartile for high-density lipoprotein cholesterol (HDL-C) values were diagnosed with abnormal levels. Results stated in boys, total cholesterol, LDL-C, and triglyceride concentrations were significantly correlated with serum ferritin levels. In both boys and girls, serum ferritin levels were negatively associated with HDL-C values, even after adjusting for all covariates. Concluded that serum ferritin levels were significantly associated with major dyslipidemia parameters, more prominently in boys than in girls, and this association represents a cardiometabolic risk factor (Kim et al., 2016).
 
Review suggested that there is strong evidence supports the concept that precursors of adult CVD begin in childhood, with obesity as an important correlate of overall CVD risk. The clearest evidence comes from autopsy studies showing that coronary atherosclerotic lesions occur in early life and are strongly associated with pediatric obesity, hypertension, and dyslipidemia. Obesity and CVD risk factors tend to persist over time. Observations from pediatric epidemiology studies over the past several decades further document that obesity, atherosclerosis, and associated risk factors begin in childhood. Lifestyle patterns, such as poor eating behavior, also begin early and influence CVD risk. The question of whether childhood obesity leads to increased adulthood CVD via increased CVD risk factors in childhood or via persistence into adulthood obesity, or both, remains unclear. However, sufficient data exist to warrant both obesity prevention and reduction in youth and adults (Nadeau et al., 2014).
 
The pathogenesis and progression of cardiovascular diseases are thought to be exacerbated by stress. Basic research indicates that the Transcendental Meditation technique produces acute and longitudinal reductions in sympathetic tone and stress reactivity. In adolescents at risk for hypertension, the technique has been found to reduce resting and ambulatory blood pressure, left ventricular mass, cardiovascular reactivity, and to improve school behavior. Research on adults with mild or moderate essential hypertension has reported decreased blood pressure and reduced use of anti-hypertensive medication. The technique has also been reported to decrease symptoms of angina pectoris and carotid atherosclerosis, to reduce cardiovascular risk factors, including alcohol and tobacco use, to markedly reduce medical care utilization for cardiovascular diseases, and to significantly decrease cardiovascular and all-cause morbidity and mortality. These findings have important implications for inclusion of the Transcendental Meditation program in efforts to prevent and treat cardiovascular diseases and their clinical consequences (Barnes & Orme-Johnson, 2012).
 | 
3. Research Methodology
 
3.1 Research approach: Quantitative Research Approach
 
3.2 Research design: Pre-experimental one group pre-post test time series research design.
 
O1 , X1 O2 X2 O3 X3 O4
 
O1 - Observation at the pre-test (Baseline)
 
X1 - Structured interventional strategy, Physical activity (skipping and walking including warm-up and rest) for 30 minutes, reduction in sedentary activity and healthy dietary habit tips by booklet and newsletter to parents.
 
O2 - Observation after 4 weeks
 
X2 Structured interventional strategy, Physical activity (skipping, walking, running, and dancing including warm-up and rest) for 45 minutes, reduction in sedentary activity and healthy dietary habit tips by booklet and newsletter to parents.
 
O3 - Observation after 8 weeks
 
X3 Structured interventional strategy, Physical activity (skipping, walking, running, dancing, and bicycling including warm-up and rest) for 60 minutes, reduction in sedentary activity and healthy dietary habit tips by booklet and newsletter to parents.
 
O4 - Observation after 12 weeks
 |

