3.10 Score Interpretation

Part I

The information on demographic data to be collected from the middle age adolescence on 15 variables and this was not scored but it is used for descriptive analysis.

Part II

These tools included; general appearance of the subjects, anthropometric measurement, and bio-physiological measurements. For Anthropometric measurements, the cut off value for height, weight, BMI and waist circumference will be calculated as per standard recommended by Indian Academy of Pediatrics (Revised IAP Growth Charts for Height, Weight, BMI and Waist circumference for 5 to 18 years old Indian Children). The blood pressure will be assessed on centile values of Indian standard (IAP).

1. Scoring for Height in cm and Weight in Kg for boys and girls

- < 25 Percentile - Below normal
- 50th Percentile - Normal
- 75th Percentile - Normal
- 90th Percentile - Below abnormal (action point to prevent obesity)
- 97th Percentile - Abnormal

2. Scoring cut off value for BMI for boys and girls

The following formula use to calculate Body Mass Index (BMI)

$$BMI = \text{Weight (kg)} / \text{Height (m}^2\text{)}$$

- < 25th percentile - Underweight
- 50th Percentile - Normal
- 75th percentile - Normal
- 85th Percentile - Overweight (action point to prevent obesity)
- 95th percentile - Obese

3. Scoring cut off value for Waist Circumference for boys and girls

- < 25th percentile - Underweight
- 50th Percentile - Normal
- 75th percentile - Overweight (action point to prevent obesity)

[figure not shown]

95th percentile - Obese

Scoring for Bio - Physical measurements

4. Scoring cut off value for systolic pressure and diastolic pressure for boys and girls

< 25th percentile - Hypotension

50th Percentile - Normal

75th percentile - Pre hypertension (action point to prevent hypertension)

95th percentile - Hypertension

Part III

It consists of 40 items. Each question had three answers with only one correct answer. When the response is correct 'one' mark was given and for the wrong answer 'zero'. The knowledge covered areas like general information of atherosclerosis, risk factors, symptoms, diagnosis and prevention of risk factors.

Scoring for Knowledge

| Sl.No.       | Areas of Knowledge         | No. of Items |  | Score     |
|--------------|----------------------------|--------------|--|-----------|
| 1            | General Information        | 9            |  |           |

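### A one-group study with a single baseline can show change, not effectiveness, yet its aim, pre-written conclusion and randomisation entry claim more

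*Protocol*

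**What the plan says.** - **Design.** Section 3.2 calls the study a "Pre-experimental one group pre-post test time series research design". The Intervention / Comparator Agent table gives the sequence as "O1 x1 O2 x2 O3 x3 O4", and its only pre-intervention point is "O1 - Observation at the pre-test (Baseline)". The comparator row reads "Comparator Agent | NIL".
- **Randomisation.** The field Method of Generating Random Sequence reads "Stratified randomization". Section 3.7.3 describes drawing three schools by lottery and then sampling sections and students. It describes no assignment to treatment.
- **Aim and definition.** Section 1.3.1 sets out to evaluate effectiveness. Section 1.5 defines effectiveness as the knowledge, activity, sedentary and dietary scores found after the intervention.
- **Conclusion.** The Brief Summary states under Conclusions: "Structured interventional strategy can improve primary and secondary outcomes among middle age adolescence". The recruitment status for India is given as not yet recruiting.
- **Limitations.** Section 1.7 names only the class range and the three schools.
- **Outcomes and entry.** The primary outcomes are BMI and physical activity at weeks 4, 8 and 12. Entry requires BMI above the 50th percentile. Section 3.10, Part II, takes its anthropometric cut-offs from the "Revised IAP Growth Charts for Height, Weight, BMI and Waist circumference for 5 to 18 years old Indian Children".

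**The concern.** Effectiveness compares what happened with what would have happened without the programme. This design supplies only the first half. A time-series argument would need several observations before the intervention, so that an existing trend could be projected forward. Here there is one, and the three later observations all follow an intervention phase.

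Under the definition in section 1.5, whatever moves the scores over 12 weeks counts as effectiveness. That includes answering the same questionnaires again, a change of school term or season, and growth. At stake is the study's main claim. A favourable change would be read as a result of the programme, in line with a conclusion written before any data. A reader searching by randomisation method would also meet an entry that the rest of the document contradicts.

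**Working it through.** **1. Sample size.** The stated 150 agrees with the sampling plan: 3 schools × 50 = 150. By class, 3 schools × 3 classes × 15 to 20 students = 135 to 180, which contains 150. Section 3.7.4 refers to a power analysis from a pilot but gives no inputs, so n = 150 is taken as given.

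**2. Can a prior trend be estimated?** A slope needs at least two observations before the intervention. The sequence has one (O1). O2 follows x1, O3 follows x2 and O4 follows x3, so none of these is an extra baseline. With no comparator, drift cannot be estimated from elsewhere.

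**3. Was anything randomised?** The random-sequence field says yes. Concealment and blinding are marked not applicable, the comparator is nil, and section 3.7.3 concerns selection into the study only. The entry describes sampling, not allocation.

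**4. What background drift does to a before-after test.** Assume a paired t-test, two-sided alpha 0.05, n = 150, independent students and zero intervention effect. Let d be the drift divided by the standard deviation (SD) of change. The test statistic then follows a noncentral t distribution with 149 degrees of freedom and noncentrality d × √150.

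| d (assumed) | d × √150 | chance of p < 0.05 |
|---|---|---|
| 0 | 0 | 5% |
| 0.05 | 0.61 | 9% |
| 0.1 | 1.22 | 23% |
| 0.2 | 2.45 | 68% |
| 0.3 | 3.67 | 96% |

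This applies to any repeated self-report, including the primary physical activity score, if retesting or the calendar moves it. The document gives no drift, so the table shows a range and is not an estimate.

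**5. BMI and growth.** Assume a natural gain of 0.3 to 0.7 kg/m² per year. Over 12 of 52 weeks that is 0.07 to 0.16 kg/m². Assume an SD of change of 0.6 to 1.0. Using the model in step 4:

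| gain / SD of change | d | significant rise or fall | significant fall |
|---|---|---|---|
| 0.07 / 1.0 | 0.07 | 13.6% | 0.25% |
| 0.12 / 0.8 | 0.15 | 44.7% | 0.008% |
| 0.16 / 0.6 | 0.27 | 90.1% | about 0% |

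Almost all of these significant results are rises. Growth therefore works against showing a BMI benefit.

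**6. BMI and the entry threshold.** Suppose the screening value is also the baseline, which the document does not say. Assume normal values centred on the chart median, no growth, and correlation R between two measurements. The mean of a standard normal variable above its median is √(2/π) = 0.798. The expected fall on remeasurement is 0.798 × (1 − R), and the SD of change is about √(2 × (1 − R)).
- R = 0.98: 0.016 / 0.200 = 0.08 SD of change, so p < 0.05 in 16% of studies.
- R = 0.90: 0.080 / 0.447 = 0.18 SD of change, so p < 0.05 in 58% of studies.

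Nearly all of these are falls, which look like benefit.

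**The case against.** The strongest reply is that the protocol hides nothing. It calls itself pre-experimental with one group, prints its observation sequence, lists the study design as other, the comparator as nil, and concealment and blinding as not applicable. The Discussion also speaks of finding out whether knowledge improves. This stands. A reader might infer from the randomisation entry that the record will pass as a randomised trial, but the neighbouring fields correct that impression. What remains is a wrong entry to be reconciled with section 3.7.3.

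A second reply concerns BMI. A reader might infer that growth will be reported as effectiveness. Step 5 shows the opposite, since growth pushes BMI upwards and masks a benefit. Section 3.10 also already refers BMI to growth charts, so part of the remedy is in place.

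Third, knowledge is where retesting is most often suspected. It is in the aim, but it is not a listed primary or secondary outcome, and no timepoints are given for it. That it is tested four times is only an inference from the observation sequence. The case therefore rests on the listed self-reports.

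None of this supplies a counterfactual. Disclosing a one-group design does not license an effectiveness claim, and the Limitations section omits the very feature that rules one out.

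**Conclusion.** The point holds as a mismatch between design and claim. With one group, one baseline and no comparator, the study can estimate change from baseline. It cannot attribute that change to the programme. The time-series label and the randomisation entry each describe a feature the study lacks, and the conclusion precedes the data.

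The possible error is material. A drift of 0.1 to 0.3 SD of change with no intervention effect gives a significant result in 23% to 96% of studies, against a nominal 5%. These figures assume a paired test, alpha 0.05, independent students and the stated drifts, none of which the document fixes. That the drift cannot be separated from an effect depends on none of them.

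Direction differs by outcome. For BMI, growth conceals benefit and regression to the mean could imitate it, the latter only if screening and baseline share one measurement. For physical activity, diet and sedentary time, retesting and calendar change are the relevant threats, and their size and direction are unknown.

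**What to change.** 1. Set the random-sequence field to not applicable and say that random sampling was used, in agreement with section 3.7.3.
2. Drop the time-series label wherever it appears, or describe the design as a one-group before-after study with repeated post-tests.
3. Delete the Conclusions line from the Brief Summary.
4. In sections 1.3.1 and 1.5, limit the claim to change from baseline. Add the missing control and the single baseline to section 1.7.
5. Analyse BMI at each visit as the age- and sex-specific z-score at exact age, or the difference from the median, on the charts already named in section 3.10. This removes average growth as the charts describe it. It does not remove regression to the mean, so item 4 still applies.

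Items 1 to 4 are wording, and item 5 uses charts already specified. The only downside is a more modest claim.

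Staggering the start across the three schools is not part of this fix. With starts at weeks 0, 4 and 8, no untreated school remains after week 8, so week 12 would still lack a concurrent comparison. Three schools also allow only 3! = 6 start orders, so a test based on that order could not give p below 1/6.
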